## 1. PROTOCOL SUMMARY (Limit to 1-2 pages)

### **Background (Issue being addressed):**

Based in part on the pivotal studies we conducted in Mali, SMC was approved by WHO as a policy for malaria control in countries with seasonal malaria transmission such as Mali in March 2012. The strategy is a highly cost-effective approach to reduce childhood mortality in these areas. Despite the huge benefit of the SMC on malaria infection and disease, the optimal approach to deliver SMC remains to be determined and there is no data on the long term effect of this strategy on the development of immunity to malaria. While fixed-point delivery (FPD) combined with non directly observed treatment (NDOT) by community health workers is attractive for the SMC implementation, it is need to be evaluated and compared to other mode of delivery. Using appropriate study designs, this project will compare differ approaches to implement SMC, and will also assess the effect of one, two and three years of SMC on malaria immunity using state of art immunology techniques and novel antigens.

### **Research Questions/Goals and Specific Objectives:**

The objectives are to identify the most effective method to deliver SMC, and to obtain information on the long term impact of SMC on malaria immunity. Specifically, i) to determine the optimal mode (fixed-point (FPD) vs door-to-door delivery (DDD); directly observed treatment (DOT) vs. non-DOT (NDOT)) and frequency (3 vs. 4 doses per season) of SMC delivery; ii) to compare quantitative measures of immunity in children who do and do not receive SMC over a three year period.

### **General Description of Study Design and Methods:**

The design is a cluster-randomized trial over three years. The target population is children aged 3-59 months old living in Ouelesseboungou district, Mali. In Year 1, villages in four sub-districts will be randomized into four groups (FPD+DOT; FPD+NDOT; DDD+DOT; DDD+NDOT). The optimal mode of delivery will be selected based on the SMC coverage during the first year,

and will then be implemented in villages of two additional sub-districts. Villages in these two sub-districts will be randomized in two groups. Children in the first group will received three rounds of SMC and those in the second group will receive four rounds of SMC to determine the optimal frequency of SMC based on the incidence rate of clinical malaria as measured by passive surveillance. Children in the four sub-districts selected in Year 1 will continue to receive three rounds of SMC in Year 2 using the optimal mode of delivery. In Year 3, children in the randomly selected sub-districts will received SMC by the optimal delivery system determined in Years 1 -2. Immune responses will be measured and compared between the children receiving SMC to a cohort of children not receiving SMC, to assess the impact of SMC on key antimalarial antibody responses over the three year period using cross-sectional surveys at the beginning and the end of the transmission season. Prevalence of malaria infection, anemia and molecular markers of *P. falciparum* resistance to SP and AQ will be measured during these cross-sectional surveys as secondary endpoints in randomly selected sample of the children.

#### **Expected Outcomes (How this study will inform implementation/scale-up):**

The anticipated outcome of the study will be a qualified optimal approach to deliver SMC in Mali, and an expanded understanding of its impact on health outcomes and antimalarial immunity.

#### **Schematic of Study Design:**

[figure not shown]

## 2. Background

More than 200 million people live in areas where malaria transmission is highly seasonal. Malaria remains a major cause of morbidity and mortality and is estimated to cause between 610 000–971 000 deaths globally per year. Sub-Saharan Africa is disproportionately affected, suffering 91% of global malaria deaths with 88% occurring in children under 5 y of age [WHO 2012]. In absence of a vaccine, simple and effective control strategies are urgently needed to reduce the malaria burden in sub-Saharan Africa. Vector control, using insecticide-treated bednets (ITNs), insecticide-treated curtains, or indoor residual spraying (IRS), can reduce mortality and morbidity from malaria substantially [Lengeler 2004], but in high transmission settings, these interventions provide only partial protection and additional control measures are needed.

We recently showed that Seasonal Malaria Chemoprevention (SMC), previously known as Intermittent Preventive Treatment of Malaria in children, reduces malaria infection and disease by more 80% in Malian children, prompting the WHO to approve SMC as policy for Sahelian countries in March 2012 [Dicko et al 2011, WHO GMP 2012]. SMC consist of of the administration of full treatment courses of an antimalarial medicine during the malaria season to prevent malarial illness with the objective of maintaining therapeutic antimalarial drug concentrations in the blood throughout the period of greatest malarial risk. The WHO recommendation states that complete treatment course of Sulfadoxine-pyrimethamine plus Amodiaquine (SP+AQ) should be given to children aged between 3 and 59 months at monthly intervals, beginning at the start of the transmission season, to a maximum of four doses during the malaria transmission season [WHO GMP 2012].

The strategy has been shown to be highly effective, safe and cost-effective for preventing malaria in children under 5 years of age in areas with highly seasonal malaria transmission such as the Sahel region in Africa [WHO GMP 2012].

Although several potential approaches can be used to implement the strategy, there is insufficient evidence to recommend a standard strategy to deliver SMC [WHO implmentation guidelines]. Two studies have compared the delivey of SMC through community health workers and health facilities in Ghana and The Gambia [Kweku et al 2009; Bojang et al 2011]. In the Gambia, higher coverage of SMC was found when SMC is delivered through community health workers

(CHW) compared to staff attached to Reproductive and Child Health trekking clinics [Bojan et al 2011] while in Ghana similar coverage of SMC was when SMC is delivered by CHW or by staff of health facilities (69% community delivery and 66% facility delivery). No study has compared the benefit of directly observed treatment compared to non directly observed treatment or door to door delivery to fixed point delivery when the strategy is delivered by the community health workers.

The pivotal efficacy studies in Mali, Senegal and Burkina Faso that have led to the evaluation and the recommendation of the strategy have assessed the efficacy of two or three treatment rounds of the SMC, and there is no data to support additional benefit provided by a 4th treatment round of SMC in the WHO recommendation. In this study we will evaluate the efficacy of 4th round of the SMC treatment against clinical malaria episodes in Mali.

## **Rationale for This Study**

Our previous studies demonstrated that SMC reduces malaria infection and disease by more than 80% in Malian children. In addition to the protective effect of the intermittent treatment other factors may have contributed to the success of these trials such as the method of treatment delivery. WHO policy to implement SMC is based on trials conducted in Mali and other sites, however, critical factors such as the optimal method of delivery that can be implemented on a country level and will achieve a similar success rate as observed in the clinical trials remained to be determined.

This study is designed to answer the primary objective, that is to identify the most effective and efficient methods to deliver SMC in Mali that is urgently needed to support SMC implementation. An optimal delivery of the strategy will make a substantial contribution toward the achievement of the goals of the US President's Malaria Initiative (PMI) and the Millennium Development Goals. The most effective method of delivery will be assessed by comparing: door-to-door delivery (DDD) or fixed point distribution (FPD) of SMC and directly observed therapy (DOT) to non-directly observed therapy (NDOT).

Another specific objective is determining the number of treatment doses. Although children participated in the trials that served as the basis to develop WHO policy received 3 treatment

doses, WHO policy suggests up to 4 treatment rounds. Taking into account the logistics associated with each treatment it is critical to determine if a 4th dose will have an additional benefit over 3 rounds of treatment.

Despite the huge benefit provided by SMC, one of the concerns is that SMC will impair the acquisition of protective immune responses, thereby increasing the risk of disease in later years. Studies conducted in Mali and other countries have compared the susceptibility to malaria among children who received the intervention over a single season and the control group during the following malaria transmission season and have found a small increase in clinical malaria among children who received the intervention [Dicko et al 2008, Dicko et al 2011, Konate et al, 20011, Wilson A et al 2011]. None of these efficacy studies have assessed the impact of SMC on immunity to malaria when given for more than one transmission season. Under conditions of long term intervention, we hypothesize that immunity to liver-stage malaria antigens (reflecting exposure to infected mosquito bites) will be similar among children receiving SMC to that of children who will not receive SMC, but immunity to blood stage antigens will be markedly decreased (reflecting protection from blood stage infection). In this proposal, children will receive intervention in a stepped wedge fashion and be followed for a period up to 3 years. We are currently studying the acquisition of immunity to malaria among children recruited at birth as part of an immuno-epidemiological (IMEP) cohort study in Ouelessebouyou, where we plan to enroll up to 2000 children who will be followed up for 5 years. We will leverage this cohort of children as a control group for the proposed intervention study. This will provide insights into the acquisition of malaria immunity and may indicate whether the cessation of longterm SMC will increase risk of subsequent malaria and warrant additional control measures.

Another specific objective of this study is to determine whether SMC will increase the spread of SP and AQ resistant parasites. In our previous study that evaluated the impact of SMC during one season on resistance to SP, there was no difference in the frequency of SP resistance markers between parasites collected in treatment and non-treatment villages. It is unknown if longer implementation of SMC will accelerate the accumulation of resistant parasites, nor the status of development of resistance to AQ. Our recent evaluation of IPTp in Tanzania, an area with widespread resistance to SP, IPTp was associated with increased placental parasite density and inflammation. The current study will allow comparing the frequencies of SP and AQ resistance

markers at the beginning of the study and during each subsequent year. The success of SMC in West Africa is due to limited spread of drug resistant parasites, however, changes in parasite population need to be monitored to ensure the effectiveness of this program.

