## 4. Study Design

### A. Detailed Description of Study Design

#### *Overall design*

The study will use a cluster randomized design over three years. Eight sub-districts will be randomly selected among the 13 sub-districts of Ouelessebouyou but excluding the sub district of the Ouelessebouyou where the IMEP cohort study is ongoing. These eight sub-districts will be randomized so that the intervention begins in four districts during the first year (Year 1), in two sub-districts in the second year (Year 2) and in two remaining sub-districts in third year (Year 3). The target population is children aged 3-59 months of age in the district of the Ouelessebouyou in Koulikoro region, in Mali.

In Year 1, the implementation of SMC will occur in four randomly selected sub-districts in Ouelessebouyou. Villages in these sub-districts will be randomized at 1:1 ratio to receive either a door-to door delivery (DDD) or fixed point distribution (FPD) of SMC. They will also be randomized to receive SMC as directly observed therapy (DOT) or non-directly observed therapy (NDOT). A census of the target population (children aged 3-59 months) will be carried out in all the selected villages prior to the intervention. During this census, blood samples will be collected in a randomly selected subset of study population to gather baseline data on cellular and humoral responses to malaria antigens, parasites prevalence and density on blood smears and frequency of the molecular markers of the resistance to SP and AQ at the start of the transmission season. The census list will be used to deliver the intervention and will be regularly updated. SMC will consist of the administration of full treatment course of sulfadoxine-pyrimethamine plus amodiaquine (SP+AQ) at monthly interval during the malaria transmission starting in August 2014. Children will be followed passively for the determination of the

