incidence of the malaria disease (uncomplicated and severe malaria). A cross-sectional survey will be carried after the third round in November/December to determine the coverage of SMC, the prevalence of the malaria parasitemia and anemia as well as humoral and cellular immune responses in a randomly selected number of children. Data collected in year 1 will be analyzed to determine the optimal delivery method (DDD+ DOT or DDD+NDOT or FPD+ DOT or FPD + NDOT) based primarily on the coverage of SMC and secondarily on the incidence of clinical malaria. The difference in SMC coverage is expected to be reflected in the incidence of clinical malaria, and the latter will be used to support the data on coverage of SMC. [Should there be no statistically significant difference between the arms in coverage and incidence of the disease, the easiest method of the delivery will be recommended for Year 2.](#)

In Year 2, SMC will be implemented using the optimal delivery system (determined in Year 1) in two sub-districts assigned during Year 2 after a census of children under 5 years of age. Villages in these two newly selected sub-districts will be randomized to receive either three or four SMC rounds during the transmission season starting in August. Baseline data on malaria parasitemia, markers of resistance to SP and AQ and immune responses to malaria antigens will be collected at baseline prior to the intervention in these two sub districts through a cross-sectional survey. In order to assess the effect of the fourth dose of SP and AQ, children will be followed passively to measure incidence rate of clinical malaria, and a cross-sectional survey will be carried out at the end of the malaria transmission season in November/December in a randomly selected sample of children to determine the prevalence of malaria infection, anemia, and humoral and cellular immune responses. Children that participated in Year 1 will continue to receive three rounds of SMC in Year 2 using the best delivery method identified in Year 1. The choice of the optimal number of doses will be based on the incidence of clinical malaria between the two arms of children in the two newly selected districts. An absolute difference of 7.5 episodes per 100 children per year will be considered meaningful.

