### **B. Planned Interim Analyses (if applicable)**

At the end of the first transmission season, data will be analyzed to determine the optimal mode of delivery by comparing primarily the coverage of SMC and secondarily the incidence rate of the clinical malaria between the four intervention arms. In addition, descriptive analysis of the baseline frequencies of the immunological parameters, and molecular markers of the resistance of *P. falciparum* to SP and AQ, will also be performed at the end of Year 1.

Data collected in Year 2 will be used to determine the optimal frequency of the SMC rounds by comparing primarily the incidence of clinical malaria and secondarily the parasite prevalence at the end of season between the 2 arms. Descriptive analysis of immunological parameters and markers of drug resistance will also be performed.

Details of the statistical methods are provided below in the final analysis plan.

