### **C. Final Analysis Plan**

*Describe statistical methods that will be used to analyze data.*

Data will be entered and verified using DataFax. The cleaned database will be exported to Stata (Houston Texas USA) or SAS for analysis. An intention-to-treat analysis will be used except for the immunological endpoints for which the exact number of the SMC treatments received will be considered.

SMC coverage will be determined using the information on the SMC card and from interview of parent or care giver and will be determined as the proportion of children who received all the treatments at all the SMC rounds during the transmission season. The proportion of children who received at least the first treatment dose of the SMC will be also estimated as secondary endpoints for SMC coverage. SMC coverage will be compared between arms and years of

interventions with 95% confidence intervals adjusted for cluster design (using cluster option in Stata for example). The DDD+NDOT arm will be considered as control group.

The census of the children will be updated at each round and at the end of the transmission season to allow a good estimation of person-time of follow-up. Cases of the clinical malaria will be recorded and the incidence rate of the clinical malaria defined as the number of clinical malaria episodes divided by total child days at risk. Children will not be considered at risk 21 days after a clinical malaria episode. Incidence rates of clinical malaria will be compared between treatment arms using generalized estimating equation to estimate the incidence rate ratio, with adjustment for age, previous SMC regimens and the lack of independence among repeated episodes in the same child.

Proportions of other secondary endpoints such as parasite prevalence, prevalence of anemia and frequency of molecular markers of resistance to SP and AQ and adverse events associated with study drugs will be estimated and compared between groups using generalized linear models with 95% confidence intervals, adjusted for cluster design and potential confounding variables such as age and use of ITN.

Differences at baseline will be compared using Chi-squared or Fisher's exact tests as appropriate for categorical variables and by analysis of the variances for quantitative variables that are normally distributed. Nonparametric tests will be used for non-normally distributed data.

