### **B. Human Subjects Considerations**

#### **i. Potential Risks**

Risks to participants in the trial are small. The trial will use only licensed and recommended drugs and does not involve any new methods. The risks to the participants are limited to those associated with the use of SP + AQ and blood sampling. Risks occasionally associated with

finger and heel pricks and venipuncture include pain and bruising at the site of the prick, and rarely infection. Use of SP +AQ can be associated with side effects of the drugs including allergy. Subjects with known allergy to the study drugs will be excluded. Over 800,000 courses of SP and AQ have been given for SMC without any report of a drug associated severe adverse event (SAE), including when surveillance is enhanced [Wilson et al 2011, Ndiaye et al submitted]. However, a potential hazard from the intervention is the possible impact of large scale drug administration over two or three years on the drug sensitivity of malaria parasites. The possibility that SMC with SP+AQ might induce resistance to these drugs in *P. falciparum* has been investigated in a number of trials of SMC. Selection of parasites carrying mutations which confer resistance to pyrimethamine or sulphadoxine has been demonstrated in some but not all studies [Wilson et al]. However, because the prevalence of parasitaemia in children who received SMC was substantially less than in the control group, the total number of parasites carrying resistance markers was less in children who had received SMC than in control children. SP has been used extensively in intermittent preventive treatment in pregnant women and has not be associated with an acceleration of resistance to SP in West Africa. Similarly the use of SP in pilot implementation in Mali was not associated with increased frequency of the molecular markers associated with resistance to SP (Dicko et al 2008). Furthermore, the potential risk of SMC with SP +AQ in inducing resistance of malaria parasite was reviewed carefully by the WHO Technical Expert Group and considered to be an acceptable risk in light of the major benefits conveyed by the intervention. Samples collected on filter paper will be tested for markers of the resistance to SP and AQ at baseline and two years after to monitor the impact of the sensitivity of the malaria parasites to the study drugs as per the WHO recommendations.

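### The contrasts named for SP/AQ resistance markers cannot separate an effect of SMC from calendar time; the randomised start year offers a concurrent comparator that the plan does not use

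*Protocol*

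**What the plan says.** The Rationale for This Study gives as a specific objective to "determine whether SMC will increase the spread of SP and AQ resistant parasites". The third specific objective in section 3.A is to monitor the impact of SMC on the markers; the French text (3.1.2) speaks of evaluating its long-term impact.

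Four places bear on how the markers are compared:

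- The Rationale says the study will allow a comparison of the frequencies of resistance "markers at the beginning of the study and during each subsequent year".
- Potential Risks says filter-paper samples will be "tested for markers of the resistance to SP and AQ at baseline and two years after".
- Planned Interim Analyses is descriptive. It plans a baseline description after Year 1 and, for Year 2, states: "Descriptive analysis of immunological parameters and markers of drug resistance will also be performed".
- The Final Analysis Plan says the "frequency of molecular markers of resistance to SP and AQ and adverse events associated with study drugs will be estimated and compared between groups", using generalised linear models adjusted for the cluster design and for confounders such as age and net use. It does not say which groups.

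On the design, Overall design (4.A) states: "These eight sub-districts will be randomized so that the intervention begins in four districts during the first year (Year 1), in two sub-districts" in Year 2 and in the last two in Year 3. For the Year 2 pair, data on parasitaemia, resistance markers and immune responses "will be collected at baseline prior to the intervention in these two sub districts".

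**The concern.** The question is causal: does SMC change the frequency of resistant parasites? A comparison of 2014 with later years in treated areas mixes any effect of SMC with whatever else changed over the same period. A background rise would look like an SMC effect, and a background fall could hide one. Potential Risks names loss of drug sensitivity under large-scale administration as a potential hazard of the intervention, so this secondary outcome carries a safety question.

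The staggered start could help. Sub-districts are randomised to begin in different years, so at a given pre-season survey some have had SMC and others have not. The protocol does not use that contrast for the markers. The sponsor's earlier one-season study, as the Rationale describes it, did compare treated with untreated villages.

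**Working it through.** **1. The sample that supplies the isolates.** Sample Size and Power gives 300 children per arm, at least 10 clusters per arm, intraclass correlation 0.01 and 5% missing data.

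- n = 300 × (1 − 0.01) / (1 − 300 × 0.01 / 10) = 297 / 0.70 = 424.3
- 424.3 / 0.95 = 446.6, against 446 stated; 4 × 446 = 1,784, as stated.

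The figure reproduces, but it is sized for SMC coverage. No size or power is given for the markers. Only smear-positive *P. falciparum* mono-infections are genotyped (Laboratory Procedures), so the isolate count depends on a prevalence that the protocol does not give.

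**2. Can any planned contrast answer the question?**

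| Contrast | Where | What differs between the sides |
|---|---|---|
| Study start v each later year | Rationale | SMC and calendar time together |
| Baseline v two years later | Potential Risks | SMC and calendar time together |
| Undefined groups, if these are the Year 1 arms | Final Analysis Plan | Delivery mode; all receive SMC |
| Undefined groups, if these are the Year 2 arms | Final Analysis Plan | Three v four rounds; all receive SMC |
| One, two or three seasons; never-treated cohort | Overall design, Year 3 | SMC exposure, but listed for immune responses and parasitaemia, not markers |

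None is a concurrent comparison of markers with and without SMC.

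**3. What the staggered start provides.** With Year 1 in 2014, completed seasons at the pre-season surveys are:

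| Survey | Year 1 group (4) | Year 2 group (2) | Year 3 group (2) |
|---|---|---|---|
| 2015 | 1 | 0 | 0 |
| 2016 | 2 | 1 | 0 |

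Pre-SMC marker sampling is explicit only for the Year 2 pair in 2015. For the other cells, the protocol summary places markers in the surveys at the start and end of the season, and Follow-up and measurement of outcomes places surveys at both times each year, without listing markers. The Year 3 paragraph does not list markers either.

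**4. Illustration of drift, all inputs assumed.** True SMC effect zero; marker frequency near 50%; n = 200 to 500 isolates per time point (200 / 1,784 = 11% to 500 / 1,784 = 28% of children surveyed); 40 villages (4 × 10); intraclass correlation 0.01.

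- DEFF = 1 + (n/40 − 1) × 0.01; SE = √(2 × 0.25 × DEFF / n); two-year shift = 2 × annual drift.
- n = 200: DEFF = 1.04, SE = √(0.52 / 200) = 0.051.
- n = 500: DEFF = 1.115, SE = √(0.5575 / 500) = 0.033.

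| Drift per year | P(two-sided p < 0.05), n = 200 | n = 300 | n = 500 |
|---|---|---|---|
| 2 points | 0.12 | 0.16 | 0.22 |
| 5 points | 0.50 | 0.66 | 0.85 |
| 10 points | 0.98 | 1.00 | 1.00 |

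A separate simulation (20,000 replicates, 89 to 535 isolates, starting frequency 20% or 40%, no clustering) applied a total drift between the two time points. The before-after test was significant in 11% to 50% of trials for 5 points and in 27% to 97% for 10 points. A concurrent test under the same drift stayed at about 5%. That simulation ignores variation between sub-districts, so a real concurrent test would be less precise.

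**5. Precision of the concurrent contrast.** For four treated v two untreated sub-districts there are C(6,2) = 15 allocations, so the smallest one-sided permutation p is 1/15 = 0.067.

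**The case against.** A reader might infer that the protocol will count any drift as an SMC effect, or that before-after is its only planned comparison. The documents support neither. No passage says a change over time will be attributed to SMC; the Rationale sentence describes what the data will allow, and the English objective is worded as monitoring. The Final Analysis Plan does foresee a modelled comparison between groups. The discontinuation rule uses absolute levels and needs no attribution.

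Nor do the documents show that drift is occurring. Potential Risks mentions SP use in pregnancy, but in the same sentence says it has not been linked to faster SP resistance in West Africa.

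The concurrent contrast has limits as well. The 2015 comparison alone cannot reach 5% in a one-sided permutation test. Parasites can move between areas of one district, which would dilute a real effect. Only drift common to all sub-districts cancels. The 2016 contrast rests on general wording.

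These points reduce the claim without removing it. Defining groups for a secondary outcome could be left to a statistical analysis plan, but this protocol itself names contrasts, and those it names do not answer the question it sets. Reading the undefined groups as the randomised arms does not help, because all of them receive SMC.

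**Conclusion.** The point holds in a limited form. The protocol asks whether SMC increases the spread of resistance, but the contrasts it names are over time, and its between-group comparison is undefined among arms that all receive SMC. Neither separates SMC from calendar time. This follows from the design and does not depend on any assumed figure.

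The size of the problem is unknown. The probabilities in the working show only how readily a drift would be detected if there were one; they are not evidence that there is one. The remedy removes bias from drift common to all sub-districts, at the price of a wide interval. The change should be made, because it is mainly a matter of wording and concerns a hazard that the protocol itself raises.

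**What to change.** In the Final Analysis Plan, define the marker comparison by randomised start year at the same pre-season survey:

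- **2015:** four sub-districts with one completed season v the two Year 2 sub-districts before their first SMC.
- **2016:** two v one v no completed seasons, provided the Year 3 pair is sampled and genotyped before starting. State this sampling in the Year 3 paragraph.

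Model marker status on completed seasons plus calendar year, with clustering at sub-district level and a small-sample correction. Report it mainly as an estimate with its confidence interval. Label the change from study start as descriptive, in the Rationale as well. Reconcile the Rationale (each subsequent year) with Potential Risks (baseline and two years after) on when markers are tested, and carry the changes into the French text.

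The cost is mostly wording, plus confirmation that filter papers from the 2015 and 2016 pre-season surveys are genotyped in every sub-district compared. If they are not, the cost includes that sampling and genotyping. The downside is an imprecise estimate from six (2015) or eight (2016) sub-districts, possibly diluted by parasite movement; the report should say so.
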